#### **8.7 Premature termination of the study**

When the trial shows a substantial amount of serious adverse events in the intervention group and patients' safety is questioned, the principal investigator can decide to terminate the study prematurely. All participants will then return to the single use regime.

## 9. SAFETY REPORTING

### 9.1 Temporary halt for reasons of subject safety

In accordance to section 10, subsection 4, of the WMO, the sponsor will suspend the study if there is sufficient ground that continuation of the study will jeopardise subject health or safety. The sponsor will notify the accredited METC without undue delay of a temporary halt including the reason for such an action. The study will be suspended pending a further positive decision by the accredited METC. The investigator will take care that all subjects are kept informed.

### 9.2 AEs, SAEs and SUSARs

#### 9.2.1 Adverse events (AEs)

Adverse events are defined as any undesirable experience occurring to a subject during the study, whether or not considered related to the investigational product. All adverse events reported spontaneously by the subject or observed by the investigator or his staff will be recorded.

#### 9.2.2 Serious adverse events (SAEs)

A serious adverse event is any untoward medical occurrence or effect that

- results in death;
- is life threatening (at the time of the event);
- requires hospitalisation or prolongation of existing inpatients' hospitalisation;
- results in persistent or significant disability or incapacity;
- is a congenital anomaly or birth defect; or
- any other important medical event that did not result in any of the outcomes listed above due to medical or surgical intervention but could have been based upon appropriate judgement by the investigator.

An elective hospital admission will not be considered as a serious adverse event.

The only expected SAE that may occur is a urosepsis after a sUTI is not recognized or acknowledged, which can occur in both the intervention and the control group.

The following situations are not considered to be SAEs and should not be reported:

- elective hospitalisation for pre-existing conditions that have not been exacerbated by trial participation.
- hospitalisation which was planned before the patient consented for study participation and where admission did not take longer than anticipated.
- medical or surgical procedure (e.g. endoscopy, appendectomy); the condition that leads to the procedure is an (S)AE, unless the condition pre-existed before trial participation.
- situations where an untoward medical occurrence did not occur (social and/or convenience admission to a hospital, palliative care, rehabilitation, overdose without occurrence of an adverse event).
- anticipated day-to-day fluctuations of pre-existing disease(s) or condition(s) present or detected at the start of the study that do not worsen.
- events that are considered to be directly linked to the standard procedures.
- events that are considered not to be linked to any study procedure.

The investigator will report all SAEs to the sponsor without undue delay after obtaining knowledge of the events.

The sponsor will report the SAEs through the web portal *ToetsingOnline* to the accredited METC that approved the protocol, within 7 days of first knowledge for SAEs that result in death or are life threatening followed by a period of maximum of 8 days to complete the initial preliminary report. All other SAEs will be reported within a period of maximum 15 days after the sponsor has first knowledge of the serious adverse events.

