## **8.2 Randomisation, blinding and treatment allocation**

Patients who sign informed consent will be randomised into the intervention or in the control group. Randomisation will be performed using the program ALEA, which is the program used in the Erasmus MC. ALEA is developed for randomisation and guarantees concealed allocation. The groups will be stratified for the participating centres, neurogenic and non-neurogenic causes for catheterization, age (16-17 years vs.  $\geq 18$  years and  $< 50$  years vs.  $\geq 50$  years old), gender, and the female patient group will be balanced for pre- and post-menopausal status. There is no ability for blinding in this trial.

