## STATISTICAL ANALYSIS PLAN for COMPaRE-trial

---

|                                     |                                          |                                        |
|-------------------------------------|------------------------------------------|----------------------------------------|
| Episodes of macroscopic hematuria   | During trial                             | Dichotomous                            |
| Hospitalisation, not study linked   | During trial                             | Dichotomous                            |
| Urethral irritation                 | During trial                             | Dichotomous                            |
| Pyelonefritis                       | During trial                             | Dichotomous                            |
| ISCQ-score (patient satisfaction)   | During trial (4 time points)             | Continuous                             |
| InCaSa-score (patient satisfaction) | During trial (4 time points)             | Continuous                             |
| SF-Qualiveen                        | During trial (4 time points)             | Continuous                             |
| Index and EQ VAS-score (QoL)        | During trial (4 time points)             | Continuous                             |
| QALYs and total costs               | During trial                             | Continuous                             |
| Patient opinion (Likert scale)      | Baseline and final visit                 | Categorical                            |
| Changes in urine cultures (S)AE     | Baseline and final visit
During trial | Dichotomous
Categorical/dichotomous |

---

---

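### Protocol 9.2.2 defines serious adverse events by seriousness, then removes some by attribution made with the arm known, so the by-arm SAE table can be filtered unequally

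*Combined protocol and SAP*

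**What the plan says.** Protocol 9.2.2 opens its definition with "A serious adverse event is any untoward medical occurrence or effect that" and lists the usual seriousness criteria. No causal link is required. It adds that urosepsis is the only SAE expected and that it may arise in either group.

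A list follows under the sentence "The following situations are not considered to be SAEs and should not be reported". The last two items are "events that are considered to be directly linked to the standard procedures" and "events that are considered not to be linked to any study procedure". Only after this list does the section require the investigator to report all SAEs to the sponsor, and the sponsor to report them to the ethics committee.

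Related text:
- Protocol 8.2: "There is no ability for blinding in this trial".
- SAP 2.2.2: control patients continue with the single-use catheter they prefer.
- SAP 6.1.4.1 and 7.1: subjects with adverse events and SAEs are summarised by treatment group, and SAEs get a separate table.
- Protocol 8.7: the termination provision begins "When the trial shows a substantial amount of serious adverse events in the intervention group".
- Protocol 9.5: no data safety monitoring board.
- Protocol 9.2.1: adverse events are defined "whether or not considered related to the investigational product", and all those reported or observed are recorded.

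**The concern.** Whether a serious event counts as an SAE should depend on what happened to the patient. Relatedness is a separate judgement. Here the judgement comes first and decides whether the event is an SAE at all, and it is made by someone who knows the arm. An SAE table built this way compares events that survived an opinion. If the opinion is formed differently in the two arms, the table can show a difference that does not exist or hide one that does. The trial's question is safety, no independent board looks at the data, and section 8.7 turns on the number of SAEs in one arm, so the SAE stream should be complete.

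**Working it through.** Neither document states an expected SAE risk or an attribution rate, so there is no plan figure to reproduce. The check sets the passages side by side and then gives an illustration on stated assumptions.

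**1. Definition against exclusion.** Take an unplanned admission, or a death, that an investigator considers unconnected with any study procedure. It meets the definition at the head of 9.2.2. Under the last item of the list it is not an SAE. Both statements cannot hold. The five earlier items (elective or pre-planned admissions, procedures as such, admissions without an untoward event, fluctuations that do not worsen) turn mainly on the nature of the event. The last two turn on attribution alone.

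**2. Urosepsis.** The section expects urosepsis as an SAE in both arms. A control-arm urosepsis attributed to the patient's usual catheterisation could be removed by "events that are considered to be directly linked to the standard procedures". The section does not say which sentence governs.

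**3. Can the rule work differently by arm?** The plan names no assessor, causality criteria or masked review for this judgement, and does not define standard procedures.
- If the term means usual single-use catheterisation, the item acts mainly on the control arm.
- If it means intermittent catheterisation as such, which protocol 6.5 describes as the same in both arms apart from the catheter, it acts on both.
- The other item, "events that are considered not to be linked to any study procedure", can remove reusable-arm events whenever the catheter is judged not to be the cause.

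Differential use is therefore possible, and its direction cannot be settled from the text.

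**4. What passes through the filter.**

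| Filtered by the two items | Not filtered |
|---|---|
| By-arm SAE table (SAP 6.1.4.1, 7.1) | Adverse event recording (protocol 9.2.1) |
| SAE reports to sponsor and ethics committee (protocol 9.2.2), and SAEs in the annual progress report (12.4) | UTI primary outcome (SAP 5.2) |
| SAE count behind protocol 8.7 | Admissions traced by record review (protocol 8.3) |
| | UTI hospitalisation, bacteraemic UTI, stricture, stones (SAP 5.3.1 to 5.3.4) |
| | Suspension under protocol 9.1 |

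**5. Illustration (risks and retention are assumed).** Let p be the true proportion of patients with an SAE, equal in both arms, and r the share kept after attribution. With 193 patients per arm (protocol 4.4), the true number is 193 × p, the reported proportion is p × r, and the false difference is p × (r in the reusable arm − r in the control arm).

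| p | True number per arm | All kept in one arm, half in the other: p × 0.5 | All kept in one arm, none in the other: p × 1 |
|---|---|---|---|
| 5% | 9.7 | 2.5 points | 5 points |
| 10% | 19.3 | 5.0 points | 10 points |
| 15% | 28.9 | 7.5 points | 15 points |

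The sign depends on which arm loses events. The last column is the arithmetic limit, not a forecast.

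The filter can also mask. Suppose the true risks are 15% (reusable) and 10% (control):
- Two thirds kept in the reusable arm and all kept in control: 15% × 2/3 = 10%, against 10%. The real 5-point difference vanishes.
- Half kept in both arms: 7.5% against 5%. The difference shrinks from 5 to 2.5 points with no differential judgement at all.

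**The case against.** The best defence is that the two items only lighten reporting and that the harms that matter are captured elsewhere. Much of the second half stands. Adverse events are asked about at every follow-up contact and recorded regardless of relatedness. SAP section 7 bases general safety evaluation on adverse events. Researchers trace admissions in the records, and the most relevant serious harms have their own definitions that do not depend on SAE status. The first half does not stand: the heading sentence removes SAE status as well as reporting, and the duty to report all SAEs to the sponsor comes after it. An event kept only as an adverse event does not enter the SAE table or count as an SAE under 8.7.

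A reader might infer more than the documents support:
- *That the SAP outcome "Hospitalisation, not study linked" cannot be collected.* It lacks an SAE route, but record review and adverse event recording remain.
- *That 8.7 is the only way to halt the trial.* Section 9.1 requires suspension on sufficient safety grounds and is not tied to SAE counts.
- *That 9.2.2 contradicts 9.2.1.* One governs adverse event recording and the other SAE status, and both can be followed. The conflict lies inside 9.2.2.
- *That the bias favours a particular arm, or that the whole safety comparison is compromised.* The direction is unknown, and the effect is on the SAE comparison.

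**Conclusion.** The point holds for the SAE comparison. Section 9.2.2 is internally inconsistent. Followed as written, it makes SAE status depend on an attribution that is unmasked, has no stated criteria and rests on an undefined term. The by-arm SAE table, SAE reporting and the SAE count under 8.7 all come after that step. This conclusion rests on the wording alone.

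The size is unknown. The false differences of 2.5 to 7.5 points assume true risks of 5% to 15% and half the events lost in one arm only; they show what the rule permits and are not estimates. If attribution were applied identically in both arms and the true risks were equal, no false difference would arise, though a real one would still be diluted.

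**What to change.** - Delete the last two items of the list in 9.2.2, or reword them so that they limit only the timing or format of submission to the ethics committee, for example a periodic line listing.
- State that every event meeting a seriousness criterion is recorded as an SAE in both arms, with relatedness in a separate field, assessed without knowledge of the arm where feasible. This also reconciles the list with the definition and the urosepsis sentence.
- In SAP 6.1.4.1 and 7.1, state that all SAEs are tabulated by arm regardless of relatedness, with any table of related events shown in addition.
- If events have already been handled under the current wording, check the adverse event record and the traced admissions against the seriousness criteria in both arms before database lock. Serious events left out during follow-up may be hard to recover in full later.

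The cost is a protocol and SAP wording change, some extra SAE forms and line listings, and the look-back where it applies. Sample size and the primary analysis are unaffected.

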### **9.2.3 Suspected unexpected serious adverse reactions (SUSARs)**

Not applicable

## **9.3 Annual safety report**

In addition to the expedited reporting of SUSARs, the sponsor will submit, once a year throughout the clinical trial, a safety report to the accredited METC, competent authority, and competent authorities of the concerned Member States. This safety report consists of:

- a list of all suspected (unexpected or expected) serious adverse reactions, along with an aggregated summary table of all reported serious adverse reactions, ordered by organ system, per study;

- a report concerning the safety of the subjects, consisting of a complete safety analysis and an evaluation of the balance between the efficacy and the harmfulness of the medicine under investigation.

#### **9.4 Follow-up of adverse events**

All AEs will be followed until they have abated, or until a stable situation has been reached. Depending on the event, follow up may require additional tests or medical procedures as indicated, and/or referral to the general physician or a medical specialist. SAEs need to be reported till end of study within the Netherlands, as defined in the protocol

#### **9.5 Data Safety Monitoring Board (DSMB) / Safety Committee**

Not applicable.

## 10. STATISTICAL ANALYSIS

### 10.1 Primary study parameters

For analysis of the results, the groups will be stratified for gender and the female patient group will be balanced for pre- and post-menopausal. Data analysis will be performed using SPSS. The primary analysis will be to assess difference between the intervention and the control groups in the sUTI rate and other adverse effects. Descriptive statistics will be used to describe baseline characteristics of participating patients in both groups. Binomial or categorical outcome measures will be analyzed using Chi-square tests and quantitative outcome variables by t-tests or Mann-Whitney U tests. Two-sided p values are calculated.

### 10.2 Secondary study parameters

Secondary outcome measurements are symptom specific and quality of life related questionnaires (PGI-I, SF-36, EQ-5D-5L), the amount of urethral damage/strictures, kidney/bladder stone formation and changes in urinary culture/urinary microbiome. The ease of use of the catheters and patients' satisfaction will be evaluated by the ISC-Q and the InCaSaQ.

**Cost-effectiveness:** For the purpose of assessing the cost-effectiveness of reusable catheters, data will be collected on medical healthcare utilization, productivity losses and quality of life of patients alongside the clinical trial. In this cost-effectiveness study, incremental costs and incremental effects of reusable catheters over single-use catheters will be assessed, with effects expressed in quality-adjusted life-years (QALYs). The cost-effectiveness study will adhere to the Dutch health economic guidelines. As such, the societal perspective will be adopted, meaning that all costs and effects will be included in the analyses, regardless to whom they accrue. The time horizon of the cost-effectiveness study will be equal to the timeframe of the clinical trial.

Uncertainty concerning the ICER, QALYs and costs will be assessed using bootstrapping, and this uncertainty will be presented graphically with the CE-acceptability curve.

Data on medical healthcare utilization (i.e. volumes) will be collected both through the hospital and by means of the iMTA Medical Consumption Questionnaire (iMCQ). The iMCQ is a generic, non-disease specific, questionnaire to be filled out by the patient, and assesses the use of a variety of medical services. Hospital records can be used to obtain information about consultations and admissions for symptomatic UTIs.

Costs of catheters will be derived from the hospital financial administration. For single-use catheters, this is equal to the purchase price of the catheters. For reusable catheters,

costs of e.g. cleaning also need to be taken into account. This will be based on the time it takes plus possibly material to prepare a reusable catheter to be used again. This information will be estimates based on e.g. observations and/or expert opinion.

The data collected on healthcare utilization will be multiplied by standard unit cost prices, which are described in the Dutch costing manual.

Data on productivity losses will be collected by means of the iMTA Productivity Costs Questionnaire (iPCQ). The iPCQ is a generic, non-disease specific, questionnaire. The iPCQ assesses productivity losses from absence from work or reduced efficiency at work and unpaid work. The data collected from the iPCQ will be monetized with hourly productivity costs derived from the Dutch costing manual. The five level version of the Euroqol 5D (EQ-5D-5L) will be used to measure quality of life of patients. The questionnaire consists of five dimensions, each with five answer levels. For cost-effectiveness studies, quality of life is often expressed in utilities, which present quality of life on a scale from 0 (death) to 1 (perfect health). The EQ-5D-5L can be used to calculate utilities using a Dutch tariff. QALYs are calculated by combining quality of life and survival. The EQ-5D-5L questionnaire will be administered at time 0, 6, 26 weeks and 52 weeks, whilst the iMCQ and iPCQ will be administered at time 6, 26 weeks and 52 weeks.

### **10.3 Other study parameters**

Other parameters such as patients characteristics, underlying (immune)diseases, hand function and mobility will be assessed with descriptive statistics.

### **10.4 Interim analysis**

Not applicable

## **11. ETHICAL CONSIDERATIONS**

### **11.1 Regulation statement**

The study will be conducted to the standards of Good Clinical Practice, in full conformance with the “Declaration of Helsinki” (version October 2013), the Dutch laws and regulations, with the WMO (“Wet Medisch-wetenschappelijk Onderzoek met mensen”) in particular.

### **11.2 Recruitment and consent**

All eligible patients will be asked to participate in this trial by their treating physician at the urological outpatients clinic of the participating centres. After a patient is well informed by the physician, a one-week period to consider his/her decision will be facilitated. After one week the researchers will discuss the decision of the patient by telephone and will answer any risen questions. When a patient decides to participate, the appointment of the first clinical visit will be planned. Signing the informed consent and randomization will be performed during this visit.

### **11.3 Objection by minors or incapacitated subjects**

Not applicable.

### **11.4 Benefits and risks assessment, group relatedness**

The possible risks of reusable catheters are increased risk of UTIs, which is the main outcome measurement of this trial. These risks may occur more often when the cleaning method is not effectively performed, which will be evaluated thoroughly during the trial. Other risks may be damage to the urethra and increased patient burden because of the cleaning procedure of the catheter. The possible advantages or benefits of reusable catheters include more patient choice, reducing fear of running out of catheters, cost saving and environmental advantages.

### **11.5 Compensation for injury**

The participating centres have a liability insurance which is in accordance with article 7 of the WMO.

The sponsor has an insurance which is in accordance with the legal requirements in the Netherlands (Article 7 WMO). This insurance provides cover for damage to research subjects through injury or death caused by the study.

The insurance applies to the damage that becomes apparent during the study or within 4 years after the end of the study.

### **11.6 Incentives**

Patients will receive a compensation for their expenses for the three or four extra consultations in the hospital. This will be 20 Euro for each consultation.

## **12. ADMINISTRATIVE ASPECTS, MONITORING AND PUBLICATION**

### **12.1 Handling and storage of data and documents**

All data will be handled confidentially and will be coded. A subject identification code list will be used to link the data to the subject. The code will not be based on the patients' initials and/or birth-date. Only the researchers involved in this trial will have the key to link the patients included in their center to their data. Handling of data will comply with the EU General Data Protection Regulation and the Dutch Act on Implementation of the General Data Protection Regulation.

### **12.2 Monitoring and Quality Assurance**

Monitoring will be done following the requirements of the Netherlands Federation of University Medical Centres (NFU) based on the ICH Good Clinical Practice guidelines. Monitoring will be carried out by qualified monitors of the Trialbureau Erasmus MC and dedicated urology research nurses. The frequency of complications due to participation in this trial are expected to be low and of low severity and not more often or severe than in the normal population. Therefore, the investigators propose to classify this study as a low-risk study. For a detailed risk and benefit assessment, please see paragraph 11.3. For low-risk clinical trials monitoring will comprise one visit per study site per year. A detailed data monitoring plan will be set up following the standardized requirements of ZonMw.

